### Data analysis

All randomized patients will be included in the analyses. A single principal analysis will be done comparing the three arms (TAH, NDVH and TLH) 12 months after the last woman has had her operation. The fact that the trial will be conducted at two centres will be taken into account during data analysis.

A Kaplan–Meier survival analysis will be done for the primary outcome which is time to recover following hysterectomy. The end-point is the actual time to recover. It will be assessed and documented at the 6-week clinic visit. Patients who have not recovered by 6-weeks will be followed-up beyond 6-weeks to detect complications and the actual time to recover. Post hoc pairwise analysis between TAH, NDVH and TLH will be done using COX regression.

Other outcomes that need follow-up; QALYs, urinary, vaginal and bowel functions will also be analysed using Kaplan Meier survival analyses. The end point for QALYs is 6-months while for urinary, vaginal and sexual function it is 1-year. Patients who do not complete follow-up in these secondary outcomes will be right censored up to their respective end-points. Post hoc pairwise analysis between TAH, NDVH and TLH will be done using COX regression. The other outcomes; operative time, anaesthesia time, postoperative hospital stay, cost, pain scores and blood loss will be analysed using Kruskal-Wallis test with post hoc comparisons. The complications will be described for each category. A fully specified Statistical Analysis Plan will be provided before opening the database.

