### Outcome measures

The primary outcome is time to recover following hysterectomy (earliest time to resume all or a combination of activities done prior to surgery; resumption of cooking, washing clothes, sexual activity and occupation). The secondary outcomes are operative time (skin to skin), postoperative hospital stay, anaesthesia time, complications (bladder injury, ureteric injury, bowel injury, convert to laparotomy, vault haematoma, blood transfusion, postoperative fever, skin wound infection, urinary tract infection, respiratory tract infection, deep vein thrombosis/pulmonary embolism, re-operation), postoperative pain and total pain medication per day per patient, QALYs, urinary, sexual and bowel function and total cost per surgery. The outcome measures are shown in Table 1.

**Table 1 Tab1:** Outcome measures and study instruments

Outcomes	Study instrument
Time to recover	Patient filled data sheet at 6 weeks
Operative time	Data sheet on operative period filled by research assistant.
Postoperative hospital stay	Postoperative data sheet filled by research assistant
Cost	Direct costs based on preoperative, operative, postoperative, 6-week and 6-month data sheets filled by research assistant Indirect costs based on preoperative, postoperative, 6-week and 6-month data sheets filled by patient
Complications	Data sheet on operative, postoperative, 6-weeks and 6-months period filled by research assistant
Anaesthesia time	Data sheet on operative period filled by research assistant
Pain scores and pain medication	Data sheet on postoperative period filled by research assistant
Blood loss/change in haematocrit	Data sheet on operative and postoperative period filled by research assistant
QALYs	Paper-based EQ-5D-3L (Sinhala/Tamil) [16]
Urinary function	ICIQ-FLUTS (Sinhala/Tamil) questionnaire [18, 19]
Vaginal and sexual function	ICIQ-VS (Sinhala/Tamil) questionnaire [20]
Bowel function	Bowel symptoms questionnaire [21]

*EQ-5D-3L* EuroQoL group questionnaire on health-related quality of life, *ICIQ-FLUTS* International Consultation on Incontinence modular Questionnaire on Female Lower Urinary Tract Symptoms, *ICIQ-VS* International Consultation on Incontinence modular Questionnaire on Vaginal Symptoms, *QALYs* Quality-adjusted life years

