### Randomization

Block randomization in multiples of three will be carried out at each study site by opening sealed envelopes containing computer-generated block randomization numbers, with block sizes of six and nine to ensure roughly equal numbers of patients in each arm at any point in the study. The patients and medical team will not be blinded to the intervention with only the statistician performing the analyses being blinded.

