### Patient selection and data collection

Eligible patients will be identified, counselled and enrolled by gynaecologists at each study centre. Before entry into the study the gynaecologist will explain to a potential patient the aims, methods, reasonably anticipated benefits and potential hazards of the study. Patient information sheets will be distributed to eligible patients and a research assistant will be available for a more detailed explanation. They will also explain to patients the potential benefit of extended long-term follow-up that would otherwise not be available and other intended benefits to the healthcare system as well as the country by participation in this research. After sufficient information, informed written consent will be obtained. Research assistants will assign enrolled participants to have either a TLH, NDVH or a TAH (Fig. 1). Patients who decline participation in the study will have standard treatment (TAH).

A preoperative questionnaire on general information, quality of life, pelvic organ function (urinary, vaginal and sexual and bowel function) and costs incurred up to surgery would be filled in by the patient while another on relevant medical information would be filled by a research assistant a day prior to surgery. Standard techniques of TLH, TAH and NDVH would be followed [15, 16]. The decision to convert to laparotomy at TLH or NDVH would be at the discretion of the primary surgeon.

Data on operative time, complications, instruments and medications used and staff allocation during surgery will be entered into a data collection sheet immediately after surgery. During the postoperative period the following information will be collected by a research assistant using a datasheet; complications, pain scores and analgesic medication and investigations. A patient-filled questionnaire will obtain costs incurred by the patient due to hospital admission. The health utility scores based on paper-based EuroQoL group health-related quality of life (EQ-5D-3L) questionnaires will be estimated on day 2 and 1 week post-surgery. (A self-addressed stamped envelope along with an EQ-5D-3L form will be provided to the patient on discharge with instructions to mail the 1-week assessment).

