### Local organisation in centres

Each centre will have a lead gynaecologist who will be the point of contact for that centre whose responsibilities will be: to establish the study locally, obtaining the required regulatory approval; to appoint and train a local research assistant; to inform all relevant local staff about the study (e.g. other consultant gynaecologists, junior medical staff, research assistants and ward staff); take responsibility for complications of the study locally; and notify the study centre of any unexpected complications due to the study. Fortnightly meetings involving gynaecologists, research assistants, junior medical staff and paramedical staff will be held at each local centre. The involved gynaecologists will identify eligible patients, explain the different surgery options to them, and ensure that study documentation has been provided and that informed consent has been obtained.

Each centre will have a local research assistant to organise recruitment of patients to the study. The responsibilities of the research assistant will be to: ensure that each participating patient has received the patient information leaflet and has given informed written consent, ensure that each participant has received all self-administered questionnaires, collect all relevant medical data on to the data sheet, keep a log of all eligible women and their recruitment status, maintain a register of all recruited patients, contact participants at relevant assessment points to obtain required data (at 1 week, 6 weeks, 3 months, 6 months and 1 year), systematic filing of study documents, data entry on to the computer database, notify the local lead gynaecologist of any problem or complication and inform local staff of progress of the study. In order to improve recruitment, research assistants will identify any eligible women in the ward who may have been missed at the gynaecology clinic.

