## Discussion

Studies in low-resource settings are hampered by financial limitations and feasibility in terms of time and collection of good quality accurate data. This protocol considers many relevant aspects concerned with the comparison of total abdominal, non-descent vaginal and total laparoscopic hysterectomy in one study for a lower-middle-income country where evidence on surgical outcomes especially in the form of randomized controlled trials are hard to come by. We believe these reasons make this protocol appealing for other researchers in similar settings.

As this is a multicentre study the involvement of multiple surgeons is inevitable and this can raise the issue of various skill levels and affect the outcome of surgery rather than a single operator. Although the issue of multiple surgeons is a limitation to the study itself, the generalisability of the results to the rest of the country would be more in our design of a pragmatic multicentre study involving multiple surgeons for each method rather than a single-centre study with a single surgeon for each method. In a study of this nature, it would not be possible to blind the patients nor the surgeons as the scars are distinct in each method. Although this is a limitation it is unavoidable and only the statistician will be blinded. The use of objective questionnaires, for patients’ as well as for assessors will also help to minimize bias [12].

The primary outcome, of time to resume usual activities, could be subject to recall bias. As it is a patient-reported outcome it has the advantage of being the best estimator of convalescence in the eyes of patients despite being subjective. Pelvic organ function is also assessed through patient-filled questionnaires as there is no objective method of assessing postoperative pelvic organ function. Although patient-reported outcomes can be subjective, validated questionnaires such as the ones used in this study make these assessments more valid and reliable. These questionnaires are the only available, non-invasive and generically applicable tools that can be used in low-resource settings.

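### For most women the primary outcome, an exact recovery day, is recalled at the 6-week visit; the protocol concedes recall bias but describes no step to reduce it, and a dated card given at discharge would be a cheap improvement

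*Protocol article*

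**What the plan says.** - **Endpoint.** Data analysis: "The end-point is the actual time to recover". It is analysed by Kaplan–Meier, with pairwise Cox regression. The Sample size calculation section sets the target difference at 7 days.
- **Source and timing.** Table 1 under Outcome measures gives the instrument for time to recover as "Patient filled data sheet at 6 weeks". Data analysis adds "It will be assessed and documented at the 6-week clinic visit", and Patient selection and data collection also places it at the 6-week clinic review.
- **Late recoveries.** "Patients who have not recovered by 6-weeks will be followed-up beyond 6-weeks to detect complications and the actual time to recover".
- **Contacts.** Local organisation in centres has the research assistant "contact participants at relevant assessment points to obtain required data (at 1 week, 6 weeks, 3 months, 6 months and 1 year"). Nothing is scheduled between week 1 and week 6.
- **Blinding.** Randomization: "The patients and medical team will not be blinded to the intervention with only the statistician performing the analyses being blinded".
- **The concession.** Discussion: "The primary outcome, of time to resume usual activities, could be subject to recall bias". The text goes on to defend patient report as the best view of convalescence. Its remark about validated questionnaires concerns pelvic organ function, and Table 1 cites no validated instrument for time to recover.
- **What women already take home.** "A self-addressed stamped envelope along with an EQ-5D-3L form will be provided to the patient on discharge", for the 1-week assessment. Women who cannot read and write are excluded.

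**The concern.** The analysis needs a date for each woman, and the difference of interest is one week. A date reconstructed weeks later carries recall error and tends to be rounded to whole weeks. Both add variance to the primary comparison.

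The recall interval also differs by arm. If the planning means are right, women after TAH recover nearer to the 6-week visit than the others do, so the quality of the recalled date need not be the same across arms.

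Time to recover is also one of the two effect measures in the incremental cost-effectiveness ratio (Economic evaluation), so the error carries into a second primary objective. An analysis plan cannot repair this later: a date that was never recorded as it happened cannot be recovered at analysis.

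**Working it through.** **1. Inputs (Sample size calculation).** TAH 28.1 days (SD 9.5), VH 21.3 (8.5), LAVH 19.7 (7.5); target difference 7 days; two-sided alpha 0.01; power 80%; loss 20%; 49 per arm.

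**2. The plan's own figure.** For TAH and VH, SD = √((9.5² + 8.5²)/2) = √81.25 = 9.014. Then n = 2 × 81.25 × (2.576 + 0.842)² / 7² = 38.7, so 39 per arm, and 39/0.8 = 48.75, so 49. The stated size is reproduced. The point challenges no stated number.

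**3. Length of recall.** The 6-week visit is day 42.

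| Group | 42 − mean (days) | Recovery after day 42 | Recovery before day 7 | Recovery between weeks 1 and 6 |
|---|---|---|---|---|
| TAH | 13.9 | 7.2% | 1.3% | about 92% |
| VH | 20.7 | 0.7% | 4.6% | about 95% |
| LAVH | 22.3 | 0.15% | 4.5% | about 95% |

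The percentages assume normal distributions, for example (42 − 28.1)/9.5 = 1.46 for TAH, giving 7.2%. So nearly all event times fall in the gap without a scheduled contact. The mean recall interval is about 7 to 8 days longer in the other two groups than in TAH (20.7 − 13.9 = 6.8; 22.3 − 13.9 = 8.4).

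**4. Illustrative power, normal approximation, 7-day difference.** Suppose recall adds independent error of SD r that is not already in the planning SD. Power = Φ(7 / (√(81.25 + r²) × √(2/39)) − 2.576).

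| Assumed r (days) | Power, 39 per arm | N per arm for 80%, with 20% loss |
|---|---|---|
| 0 | 80% | 49 |
| 2 | 78% | 52 |
| 3 | 75% | 55 |
| 4 | 71% | 59 |
| 5 | 66% | 64 |
| 7 | 55% | 79 |

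Rounding to whole weeks alone corresponds to r = 7/√12 = 2.0 days.

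**5. Illustrative power, log-rank simulation at the published means.** Normal recovery times, 39 per arm, two-sided 0.01. Ranges are across repeated runs of 2,000 to 4,000 trials per scenario.

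| Assumed r (days) | TAH vs VH (difference 6.8) | TAH vs LAVH (difference 8.4) |
|---|---|---|
| 0 | 74–78% | 97% |
| 2 | 73–75% | 96–97% |
| 4 | 66–67% | 93% |
| 6 | 54–56% | 84–85% |
| Weekly rounding | costs about 1–4 points | 96% |

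The TAH vs VH start below 80% is not a recall effect. With no error, the formula in step 4 gives 77.5% at 6.8 days instead of 7. The LAVH column depends on the larger published difference of 8.4 days.

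**6. Differential recall.** If recall shifted one arm by an assumed 1 or 2 days relative to the other, with no true difference, the two-sided type I error would be 2.0% or 5.5% against the planned 1% (SE = 9.014 × √(2/39) = 2.04 days). The documents give no basis for any particular shift.

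**The case against.** The case on the other side is substantial, and much of it stands.

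- **The limitation is disclosed.** The protocol neither misstates nor contradicts its collection method. That is right: this is a design improvement, not an error. Disclosure does not reduce the bias, however.
- **The power figures may double-count.** The planning SDs are observed values from a published study, and the protocol does not say how that study recorded recovery. If it too relied on recall, the extra loss could be nil. The figures therefore show sensitivity only.
- **Large losses need unsupported inputs.** Error SDs of 4 to 6 days have no support in the documents. The best-motivated sizes, 2 days or weekly rounding, cost little, and the laparoscopic contrast has power to spare at the published means. A reader might infer that recall leaves the trial underpowered; the documents do not show that.
- **A missed visit is not a missing outcome.** A reader might infer that a woman who misses the 6-week visit yields no recovery date. Compliance issues promises active contact to limit loss to follow-up, Local organisation in centres has research assistants contact women at 6 weeks, and those not yet recovered are followed further. What such contact may bring is a later recall.
- **The card does not cure lack of blinding.** An unblinded woman still judges when she has recovered, and may fill in the card late. It would be wrong to credit the card with removing the possible shift in step 6.
- **The existing envelope does not serve.** It is for the 1-week form, before most recoveries.
- **Recruitment has begun.** The first randomisation was on 1 August 2016, so only women not yet discharged could receive the card.
- **The data sheet is not shown.** It may already ask for a date per activity, but it would still be filled in at 6 weeks.

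None of this changes the central fact that most primary event times are recalled rather than recorded.

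**Conclusion.** The point holds as a cheap, worthwhile improvement. For most women the primary event time is a retrospective report made 2 to 3 weeks after the expected recovery day, with no scheduled contact in the interval when over 90% of recoveries are expected. The protocol names the resulting bias and describes nothing to reduce it.

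The size is uncertain. It rests on assumed, independent, normal recall error added to SDs that may already include some. On that footing, TAH vs VH loses about 2 to 3 points of power at an error SD of 2 days, roughly the same with weekly rounding, and about 10 to 20 points at 4 to 6 days. TAH vs LAVH remains above 80% in all these scenarios at the published means. The sample size of 49 per arm is unaffected.

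**What to change.** Give each woman at discharge a one-page card listing the activities named under Outcome measures (cooking, washing clothes, sexual activity, occupation). She writes the date on which she first resumed each one. She brings the card to the 6-week visit or posts it in its own stamped envelope.

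In the protocol or analysis plan, state that:

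- the card date is the primary source;
- the date recalled at 6 weeks is used where the card is missing;
- the source is recorded for every woman;
- a sensitivity analysis by source is reported.

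Separate dates per activity also help because the Abstract defines recovery by all usual activities, while Outcome measures allows all or a combination of them. With a date for each, whichever definition is settled can be applied.

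Cost: printing and postage, a short instruction by the existing research assistant, a small burden on patients and a minor amendment. No extra visit or staff is needed. Because recruitment has begun, the trial will mix sources. Block randomisation should keep the mix roughly balanced across arms at the point of change, and recording the source lets it be examined.

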#### Secondary objectives

To determine quality of life following TLH, NDVH and TAH using QALYs.To evaluate the urinary, sexual and bowel function following hysterectomy.

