### Description of study instruments

The validated paper-based Sinhala and Tamil EQ-5D-3L questionnaire will be used to obtain health utility scores. The EQ-5D-3L is a generic multi-attribute utility system, which assess health-related quality of life on five dimensions (mobility, self-care, usual activities, pain/discomfort, anxiety/depression) [17]. Based on the responses a woman will be placed in to one of 243 (3^5^) mutually exclusive health states, and a value for each of these has previously been estimated with ‘0’ being equivalent to dead and ‘1’ being equivalent to perfect health on a utility scale based on interviews. EQ-5D 3L questionnaires will be administered 1 day preoperatively and on postoperative day 2, 1 week, 6 weeks, 3 months and 6 months postoperatively. Each woman’s QALYs will be calculated using the utility score and the time spent on the particular health state. A utility value table specific to Sri Lanka will be used to calculate QALYs [18].

Urinary and sexual function will be assessed by the validated Sinhala and Tamil translations of International Consultation on Incontinence Modular Questionnaire on Female Urinary Tract Symptoms (ICIQ-FLUTS) and Incontinence Modular Questionnaire on Vaginal Symptoms ICIQ-VS which were obtained from the International Consultation on Incontinence (ICI) [19–21]. Bowel symptoms will be assessed by a questionnaire based on a study done by Tharkar et al. [22]. These questionnaires will be used preoperatively, 6 months and up to 1 year post-hysterectomy to detect changes in pelvic organ function.

Postoperative pain evaluation will be done using numeric pain rating scale (NRS) [23], asking the patient to indicate the intensity of current, best, and worst pain levels over the past 24 hours on a scale of 0 (no pain) to 10 (worst pain imaginable). The average of the three ratings; average, best, and worst will be used to represent the patient’s level of pain over the previous 24 hours. To allow direct comparison of pain medication a modified World Federation of Societies of Anaesthesiologists (WFSA) analgesic ladder will be used [24].

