### Economic evaluation

The economic evaluation will take societal perspective and will include direct costs related to utilization of healthcare resources in the hospital and indirect costs which are borne by the patient. A micro-costing approach will be adopted to calculate utilization of hospital resources from the time of presentation to the gynaecology clinic up to six months after surgery. Incremental cost-effectiveness ratios (ICER) will be obtained by calculating the incremental costs divided by the incremental effects (time to recover and QALYs gained) for the intervention groups (NDVH and TLH) over the standard care (TAH) group.

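### QALYs and pelvic organ function are assigned Kaplan-Meier and Cox analyses although no event is defined for them, so both secondary objectives lack a valid between-arm comparison

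*Protocol article*

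**What the plan says.** The Data analysis section assigns Kaplan-Meier to the primary outcome, time to recover, and extends it: "Other outcomes that need follow-up; QALYs, urinary, vaginal and bowel functions will also be analysed using Kaplan Meier survival analyses". The end points are then given: "The end point for QALYs is 6-months while for urinary, vaginal and sexual function it is 1-year". Bowel function appears in the first list but not in the second. Incomplete follow-up is handled so: "Patients who do not complete follow-up in these secondary outcomes will be right censored up to their respective end-points". The between-arm test is: "Post hoc pairwise analysis between TAH, NDVH and TLH will be done using COX regression".

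Description of study instruments says what these outcomes are. For QALYs: "Each woman’s QALYs will be calculated using the utility score and the time spent on the particular health state". For the urinary, vaginal/sexual and bowel questionnaires: "These questionnaires will be used preoperatively, 6 months and up to 1 year post-hysterectomy to detect changes in pelvic organ function".

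The Secondary objectives rest on exactly these outcomes: "To determine quality of life following TLH, NDVH and TAH using QALYs.To evaluate the urinary, sexual and bowel function following hysterectomy". The Economic evaluation section uses QALYs separately, by "calculating the incremental costs divided by the incremental effects (time to recover and QALYs gained").

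**The concern.** Kaplan-Meier and Cox regression need an event and the time at which it occurs. Time to recover has both. A QALY total is one accumulated quantity per woman, and a symptom score is a level recorded at a visit. The reason the article gives for putting them under survival analysis is that they need follow-up, but repeated measurement is not the same as time-to-event data. In the same paragraph other measured quantities, such as pain scores and cost, go to a Kruskal-Wallis test.

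At stake is the between-arm evidence on quality of life and on urinary, sexual and bowel function. The Background presents the shortage of such data as a reason for the trial, and the stated hypothesis names both. This is not a detail left to the later analysis plan, because the article itself fixes the method.

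**Working it through.** **What each outcome offers a survival analysis**

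| Outcome | Nature (Description of study instruments) | Stated end point (Data analysis) | Event defined |
|---|---|---|---|
| QALYs | utility accumulated over time | 6 months | none |
| Urinary, vaginal/sexual function | scores before surgery, at 6 months and up to 1 year | 1 year | none |
| Bowel function | scores at the same times | not named | none |
| Time to recover | days until activities resume | actual time to recover | yes |

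**Reading 1: calendar time, with the end point as the event.** The sample size section gives 49 women per arm with 20% loss, so 49 × 0.8 = 39.2, about 39 completers per arm. All have time 6 months, and dropouts are censored before it. Let n1 and n2 be the numbers still at risk, n = n1 + n2, and d = n the number of events at that single time.

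- Expected events in arm 1: E1 = d × n1/n = 78 × 39/78 = 39. Observed: 39. Difference: 0.
- Log-rank variance: d × (n1/n) × (n2/n) × (n − d)/(n − 1) = 78 × 0.5 × 0.5 × 0/77 = 0.
- Cox regression fitted to 39 + 39 such women: log hazard ratio 0, p = 1.

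E1 equals n1 for any n1 and n2, so even unequal dropout does not enter the test. Both Kaplan-Meier curves stay at 1 until 6 months and then fall to 0. No utility value appears anywhere in the calculation. If actual visit dates were used instead of nominal ones, the comparison would be of visit scheduling.

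**Reading 2: the QALY total as the time axis.** The event is completing 6 months, and a dropout is censored at the QALYs accrued so far. A woman in better health accrues QALYs faster, so at a given dropout date she is censored at a higher value. Censoring is then related to the outcome even when dropout dates are random.

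The article gives no utilities, so the size of the bias needs assumptions. One simulation assumed mean utilities of 0.75 before surgery, 0.45 on day 2, 0.55 at 1 week, 0.75 at 6 weeks, 0.82 at 3 months and 0.85 at 6 months in the reference arm, with temporary gains of up to 0.10 in the other arm. It assumed 20% random dropout after the 1-week, 6-week or 3-month assessment.

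- Kaplan-Meier mean against true mean: 0.3859 against 0.3859 in one arm, 0.4066 against 0.4066 in the other.
- The near-zero bias has a reason. Three months at a utility of 1 is 0.25 QALY, so every dropout is censored at or below 0.25, while completers average about 0.39. Censoring is almost over before the first event.
- Varying the dropout timing and the spread of utilities gave a bias of about 0 to 4% of the mean QALY.

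Cox regression on this axis estimates a hazard ratio for reaching a QALY total. It does not estimate a difference in QALYs.

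**Reading 3: an unstated threshold event for the function scores.** With two postoperative assessments, such an event could be placed only before 6 months or between 6 months and 1 year. The article gives no threshold.

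**The case against.** The strongest defence is that the end points can be read as follow-up horizons, with the event (say, a set deterioration) left for the fully specified analysis plan that the article promises before the database is opened. On that reading the event is undefined rather than impossible. This has some force for the function scores, but it does not rescue the text. The article says the questionnaires are there to detect changes, and a threshold event would answer a different question. For QALYs no natural event exists. Specifying the stated method more fully would keep the problem.

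Several stronger conclusions are tempting, and the article does not support them:

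- *That QALYs could not be compared at all, or that the test has no power on any reading.* This holds for the calendar-time reading. With a QALY axis a rank-type comparison remains possible.
- *That the comparison would be seriously biased.* The bias is real in principle, but no large size is shown. The simulations covered random dropout only, so they do not rule out more under health-related dropout.
- *That the cost-effectiveness result is lost.* The Economic evaluation section takes incremental QALYs directly, without Kaplan-Meier or Cox regression, so the ICER point estimate stands.
- *That preoperative values will be ignored.* The article is silent on covariates, and silence is not exclusion. Covariate choice and imputation method are commonly left to the analysis plan. The precision gained by baseline adjustment is therefore no measure of this defect.

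**Conclusion.** Wrong as written, within a limited scope. The article prescribes a time-to-event analysis for outcomes without events. Taken literally, it carries no information on quality of life (log hazard ratio 0, p = 1, by construction), and the same argument applies to function scores at a fixed 1-year time. On the kindest reading, QALYs get a rank-type comparison on a hazard-ratio scale that does not answer the secondary objective. Its informative censoring has a bias of about 0 to 4% of the mean QALY under assumed utilities and random dropout, and of unknown size otherwise.

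Both secondary objectives therefore lack a valid planned comparison between arms. The type of analysis chosen for time to recover, the sample size, the data collection and the ICER point estimate are not affected. The conclusion on the literal reading needs no assumption about utilities. Only the bias figures do.

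**What to change.** Reword the Data analysis section and carry the change into the analysis plan before the database is opened:

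- **Time to recover:** keep Kaplan-Meier and Cox regression, and restrict them to this outcome.
- **QALYs:** compute the area under each woman's EQ-5D-3L utility curve to 6 months. Compare arms by regression on arm, centre and the preoperative utility already collected, and report mean differences with 95% confidence intervals (bootstrap).
- **Urinary, vaginal/sexual and bowel function:** compare the 6- and 12-month scores as continuous or ordinal outcomes, for example by a mixed model with baseline score and centre. Name the assessment time for bowel function.
- **Incomplete follow-up on these outcomes:** treat it as missing data and delete the censoring sentence.

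Other suitable methods for continuous or ordinal scores would also serve. What matters is that the estimate is a difference in QALYs or scores. The change costs wording and a little analyst time. It needs no new data, visits or patients. Because it departs from the published text, it should be recorded as a change made before the data were seen.
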